#### Pre-intervention resources

Pre-intervention resources will include the pre-course manual, ‘meet and greet’ forum and the reading list. Participants will be able to complete a self-diagnostic tool to identify and reflect on their current IGA engagement and barriers to confident gait-related practice.

#### Intervention components

The intervention will be a stand-alone, post-graduate level educational event delivered fully on-line. It will employ the delivery of weekly on-line plenary sessions incorporating active learning — synchronous on-line problem-based learning sessions and seminars integrating elements of experimental learning within the learning community. These sessions will be delivered by experienced educators and clinicians working in the instrumented gait analysis laboratories, with a track record of delivering education within the field of gait analysis and paediatric neurodisability. Educators will be approached via email by the lead researcher. Content of the intervention will encompass an array of gait analysis methods and an overview of equipment currently used in the clinical practice. This will include but will not be limited to clinical outcome measures, measurement software, videography techniques and setup, 3-dimensional motion laboratory equipment, and laboratory setup (examples of Vicon and Codamotion Systems). Intervention will comprise of weekly tasks (asynchronous) to facilitate revision and application in practice and formative assessment/feedback opportunities (short knowledge quizzes, open questions within the discussion forum) to support learning autonomy and facilitate participant’s recall and self-regulation. Table 2 provides an indicative number of hours for each activity to give an overall picture of the workload a participant would be expected to undertake.

**Table 2 Tab2:** Intervention learning format and an indicative number of hours for each activity

Learning format	Module-specific breakdown	Hours
**Content**	Seminars/PBL sessions	5
	Lectures/plenary	13
	On-line live forum interaction	2
**Student/peer learning**	Discussion/group work	4
**Student independent learning time**	Pre-session preparations (total)	4
	Completing assessments (incl. formative)	3
**Total study hours (6 weeks total)**		**31**
**Pre-course preparation**		2–4

The intended learning outcomes (ILOs) have been designed and benchmarked against the QAA Statements Physiotherapy (2001) Academic Content.

Academic content is as follows:Demonstrates an understanding of the interdisciplinary knowledge that underpins gait analysis practice including elements of human anatomy, biomechanics, and gross motor development: C1Demonstrates an understanding of the principles of typical gait pattern and how movement patterns are likely to be affected by some of the childhood diseases: C1Demonstrates an understanding of the available measurement technologies and the principles on which they are based: C1

Disciplinary skills are as follows:4.Applies variety of gait assessment methods in context of own practice and service delivery: B1 and C25.Uses the gait analysis outputs in clinical practice to aid treatment decision-making and measurement — in line with clinical reasoning paradigms and evidence-based practice: A1, B1, and C26.Communicates assessment findings and gait-related decision-making effectively with multidisciplinary team, patients, and families: A2, A3, B2, and C2

Attributes are as follows:7.Cultivates an individualised, patient-centred approach to assessment and treatment planning: B28.Reflects on own practice to identify the needs within own role and wider aspects of service delivery: A3, A4, and B2 (health and social care equivalent B4)9.Demonstrates a creative drive to implement the knowledge and skills, improve own practice, and support development of others: A3, A4, and B2 (health and social care equivalent B3)

### Behaviour change techniques (BCT)

Utilisation of the BCT taxonomy [20] will support refinement of the targeted behaviours. It will also support the process evaluation analysis to gain understanding of how the change is expected to take place [21] and related barriers and facilitators of implementing the feasibility trial. To support knowledge transfer, several behaviour change techniques will be used in the intervention content.

Prior to the course, participants will gain access to a diagnostic session to identify potential internal and/or external barriers to their gait-related practice. They will be encouraged to set their personal and service goals and will be supported in making plans for delivery. Participants will share their plans and progress as part of the evaluation process.

A variety of synchronous (problem-based learning sessions) and asynchronous resources (lectures, reading links and podcasts) will incorporate instruction on how to perform new or refined gait-related practice behaviours. These resources will also support shaping of the participant’s knowledge through instruction and demonstration on how to perform the behaviours and setting clinically oriented practical tasks focusing on the behaviour. Throughout the course, participants will be provided strategies to support behaviours through associations such as regular prompts and cues, ideas on restructuring of their clinical environment to improve their gait assessment quality and techniques, or through objects which could be added into their environment (such as outcome measure templates — digital and/or printed). A virtual learning community, created through group chats and discussion forums, will aim to support emergence of the identity associated with changed behaviours.

Figure 3 outlines the simplified logic model of the study.

**Fig. 3 Fig3:**
[figure not shown]
Feasibility RCT study logic model

#### Control group intervention

To compare the effects of the intervention against usual practice, participants allocated into the control group will be asked to continue with their usual practice. At the point of enrolment, the control group will gain access to the virtual learning environment and receive basic orientation resources, but no training or guidance will be offered during this time. Participants in the control group will be asked to complete the same measurements as those in the intervention group and at the same timepoints (Table 1). The control group will be offered the full intervention after the completion of the third round of assessments. Provision of educational content and its timing in the control group were reviewed during the stakeholder focus groups including of clinicians and educators.

#### Outcome measures

Outcome measures were grouped as primary outcome measures (trial feasibility-related outcomes) and secondary outcome measures (trial research-related outcomes) collated in Table 3.

**Table 3 Tab3:** Summary of primary and secondary outcome measures, hypotheses and analysis methods planned in the study

Variable/task	Hypothesis/target	Outcome measure	Method of analysis
***Primary***			
Recruitment	Study will recruit 24 participants	Number of participants	Descriptive statistics
Retention	Study will retain 75% of sample	Number of participants	Descriptive statistics
Engagement	The average proportion of completed VLE items will be ≥ 66%	Average proportion of completed VLE items	Descriptive statistics
***Secondary***			
Knowledge	EG will have improved knowledge scores relative to CG EG will increase knowledge scores EG will maintain knowledge scores	MCQ test	Effect sizes and 95% CIs from repeated measures ANOVA test and Kruskal–Wallis *H*-test
Skills	EG will have improved practical skills scores relative to CG EG will increase practical skills scores EG will maintain practical skills scores	OSCE	Effect sizes and 95% CIs from repeated measures ANOVA test and Kruskal–Wallis *H*-test
Attitudes	EG will have improved gait-related practice behaviours	Questionnaires: Self-reported knowledge and confidence, practice change, practice change planning, beliefs, semi-structured interviews	Effect sizes and 95% CIs from repeated measures ANOVA test Framework method for qualitative data (Ritchie 2014)
Satisfaction	EG will demonstrate a high satisfaction rate	Satisfaction questionnaire	Descriptive statistics

*EG* experimental group, *CG* control group, *VLE* virtual learning environment, *MCQ* multiple-choice question, *OSCE* observed standardised clinical examination

Recruitment will be determined as feasible if study is able to recruit 24 participants within 4 months [22, 23]. Retention rates will be considered at two stages: (1) from expression of interest to consent — it will be deemed feasible if greater than 50%, and (2) from consent to course completion — it will be deemed feasible if greater than 75% [24, 25]. Additionally, engagement (participants’ interactions with an online system) data will be collected during intervention via the analytics tools in the QMUL Virtual Learning Environment which log the detail of activity access, time, and completion for each component. These analytic tools are part of the general-purpose dashboard and provide an algorithmic representation of student online behaviours based on whether the behaviour occurred and for how long, rather than quality of these behaviours. Previous studies show that these analytics have been positively correlated with student performance [26–28]. It will be deemed feasible if the average proportion of completed learning sessions and tasks will be ≥ 66%.

Secondary outcomes are as follows: knowledge, skills, attitudes, and satisfaction will be collected via online questionnaires (SurveyMonkey) and during skill tests (OSCE). Knowledge, skills, and attitudes will be collected at three timepoints (Table 1).

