##### Post intervention (immediately after 6-week intervention)

Questionnaire including attitudes (planning practice change, implemented practice change, beliefs), confidence (self-rated), knowledge (self-rated and multiple-choice question test), and satisfaction (experimental group only)OSCE of a different patient case (scored against the same criteria as at baseline)

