##### Re-test (4-month post-intervention)

Questionnaire attitudes (planning practice change, implemented practice change, beliefs), confidence (self-rated), and knowledge (self-rated and multiple-choice question test)OSCE of a different patient case (scored against the same criteria as at baseline)

Knowledge and skills retention as well as attitudes will be measured between timepoints, with a focus on changes between baseline and immediately post intervention and at 4-month follow-up. Satisfaction questionnaire will contain 28 items, each assessed on a 5-point Likert scale, related to the relevance and scientific quality of the content, the educational structure, and delivery. Satisfaction feedback will be collected immediately after intervention delivery (experimental group).

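### Two of the three knowledge and skills hypotheses concern the experimental arm alone, where change over time cannot be separated from OSCE case difficulty or MCQ test effects

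*Protocol article*

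**What the plan says.** Table 3 of the protocol article gives three hypotheses each for knowledge (MCQ test) and skills (OSCE).

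- **Between arms, listed first:** "EG will have improved knowledge scores relative to CG" for knowledge and "EG will have improved practical skills scores relative to CG" for skills.
- **EG alone, listed second and third:** "EG will increase knowledge scores EG will maintain knowledge scores" for knowledge and "EG will increase practical skills scores EG will maintain practical skills scores" for skills.

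One method entry covers all three hypotheses in each row: effect sizes with 95% CIs from repeated measures ANOVA, together with a Kruskal–Wallis test.

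On measurement, the Outcome measures section states "Knowledge, skills, and attitudes will be collected at three timepoints (Table 1"). The post-intervention assessment is an "OSCE of a different patient case (scored against the same criteria as at baseline"), and the 4-month re-test is described in the same terms. The 4-month questionnaire again covers "knowledge (self-rated and multiple-choice question test"), as do the two before it. The text does not say whether the MCQ items repeat. The Re-test section adds that "Knowledge and skills retention as well as attitudes will be measured between timepoints", with the emphasis on change from baseline.

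Under Control group intervention, controls take the same measurements on the same schedule as EG. The Abstract names a two-way mixed ANOVA, and the analysis section plans a preliminary analysis of between-group differences. All analyses are declared exploratory.

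**The concern.** A hypothesis that EG scores rise, or hold, over time is answered by comparing EG with itself at different visits. Here the instrument also changes, or is met again, between those visits. For the OSCE, visit and patient case move together. Scoring every case on the same criteria does not make the cases equally hard, so EG data alone cannot tell learning from an easier case, or forgetting from a harder one. For the MCQ, if items repeat, the change includes practice; if they do not, it includes any difference in difficulty between forms.

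An easier second case could therefore be reported as learning, and a harder 4-month case as lost skill. This matters to a feasibility trial because its objectives include judging whether the outcome measures suit the study aims and defining the sample size for the definitive trial. An EG-only effect size carried into either task would bring the test effect with it.

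**Working it through.** The plan states no figure to reproduce on this point: no SD, correlation, effect size or expected shift. The check is a simple model followed by an illustration under stated assumptions.

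**1. What each contrast estimates.** In SD units, let τ be the course effect on change between two visits, and p the shift in score between those visits due to case difficulty, test form or repetition, assumed equal in both arms.

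- Expected EG change = τ + p
- Expected CG change = p
- Expected EG−CG difference in change = (τ + p) − p = τ

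| True τ | Shift p | EG-only change | EG−CG difference in change |
|---|---|---|---|
| 0 | 0.3 | 0.3 | 0 |
| 0 | 0.5 | 0.5 | 0 |
| 0.5 | −0.3 | 0.2 | 0.5 |

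The same holds for *maintain*. Suppose nothing is lost after the course (τ = 0 from post-intervention to 4 months) but the 4-month case is 0.3 SD harder. EG falls by 0.3 SD, CG falls by 0.3 SD, and the difference in change is 0.

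**2. How often a pure test effect could look like an increase.** Inputs from the protocol article: 12 per arm (Sample size), and 75% retention (Table 3), which gives 0.75 × 12 = 9. Assumptions: p = 0.2, 0.3 or 0.5 SD, and correlation ρ between visits of 0.5 or 0.7. As a yardstick, take a paired t-test in EG at two-sided 5%; the plan does not specify such a test.

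- SD of change: s = √(2(1 − ρ)), so s = 1.00 at ρ = 0.5 and 0.77 at ρ = 0.7
- Noncentrality: p√n / s; for example, n = 12, ρ = 0.5, p = 0.3 gives 0.3 × 3.46 / 1.00 = 1.04
- Probability of a significant increase when τ = 0: upper tail of the noncentral t beyond the 97.5% point on n − 1 degrees of freedom; in the example, 15.6%
- 95% CI half-width, EG-only change: t(n − 1) × s / √n
- 95% CI half-width, EG−CG difference in change: t(2n − 2) × s × √(2/n)

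| n per arm | ρ | p = 0.2 | p = 0.3 | p = 0.5 | Half-width, EG only (SD) | Half-width, EG−CG (SD) |
|---|---|---|---|---|---|---|
| 12 | 0.5 | 9.2% | 15.6% | 35.3% | 0.64 | 0.85 |
| 12 | 0.7 | 12.7% | 23.2% | 53.2% | 0.49 | 0.66 |
| 9 | 0.5 | 7.7% | 12.2% | 26.2% | 0.77 | 1.00 |
| 9 | 0.7 | 10.1% | 17.5% | 39.9% | 0.60 | 0.77 |

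With no learning and no shift, the upper-tail rate would be 2.5%. The last two columns show the price of the controlled contrast: its interval is wider, but it is centred on τ when the shift is common to both arms.

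**The case against.** The strongest reply is that the plan already contains the right analysis. The first hypothesis in each row is between arms, controls are tested in parallel, the model has group and time as factors, and the analysis section speaks of between-group differences. Nowhere is an EG-only test specified. On this view the three lines in Table 3 are loose labels for the group contrast, the early change and the later change in one model. The outcomes are also secondary and exploratory, and none of the recruitment, retention and engagement criteria uses them.

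Most of that stands. It protects the first hypothesis fully and keeps the severity low. It does not settle the other two: they name EG alone, sit beside a line that does name the control group, and share a method entry that does not say which contrast answers which hypothesis.

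A reader might infer more than the documents support:

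- **That the knowledge and skills comparison as a whole is uncontrolled.** It is not; the between-arm hypothesis is unaffected.
- **That maintenance will be concluded from a non-significant fall.** No such rule is stated; the plan is effect sizes with CIs.
- **That the same MCQ items are reused.** The text does not say.
- **That the absence of case matching or test equating is itself a fault.** A condensed article commonly leaves such detail to the full protocol.
- **That the percentages in the table are this trial's error rates.** They rest on assumed shifts and correlations and on a test that the plan does not name.

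**Conclusion.** The point holds in a narrow form and at low severity. For knowledge and for skills, two of three hypotheses are worded as EG-only change, and EG data alone cannot separate that change from OSCE case difficulty or from MCQ repeat-test or form effects. Whatever the shift is, it enters the EG-only change in full; the 0.2 to 0.5 SD range is an assumption. It cancels in the EG−CG difference in change provided it is common to both arms. That would fail if, for example, a harder case cost untrained participants more than trained ones. Nothing here undermines the between-arm hypotheses or the feasibility decision.

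**What to change.** In Table 3, for both knowledge and skills:

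- restate *increase* as the EG−CG difference in change from baseline to post-intervention;
- restate *maintain* as the EG−CG difference in change from baseline to 4 months, shown with the EG−CG difference in change from post-intervention to 4 months;
- take each, with its 95% CI, from the group-by-time contrasts of the planned two-way mixed ANOVA;
- present EG-only means and changes descriptively.

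The *maintain* contrast should be a difference in change, because a difference in level at 4 months is not a group-by-time term and carries any baseline imbalance. Imbalance is plausible with 12 per arm and colleagues from one trust allocated together.

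The cost is wording only: no new data, participants or model. The small downside is that the EG-only statements are no longer tested as hypotheses, and the between-arm intervals are wider (0.66 to 0.85 SD against 0.49 to 0.64 SD half-width at 12 per arm, under the assumptions above).

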### Trial design

This will be a two-arm feasibility randomised controlled trial with an experimental and control group. The 6-week on-line intervention delivered as part of the trial is a stand-alone, post-graduate level educational course called Virtual Gait Analysis Course for Paediatric Physiotherapists (VGAPP). Eligible physiotherapists who consent to take part in the study will be randomly allocated into experimental and control groups. A repeated measures design will be adopted, whereby participants will complete outcome measures at baseline, immediately after the intervention, and at 4 months. This will include collection of feedback as part of a full process evaluation.

The trial will be determined feasible if a priori set criteria based on primary outcome measures and included in the process evaluation will be achieved at or above agreed levels (see the ‘Outcome measures’ section of ‘Methods’). After conducting and reviewing outcomes of the full evaluation process, the decision about delivery of the definitive trial will be made.

Figure 1 shows the study flow diagram, and Table 1 indicates the schedule of enrolment, intervention, and outcome measures [18].

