### Sample size

Considering the study objectives and recommendations, the target sample size will be of a minimum 12 participants per trial arm; therefore, a minimum of 24 in total is anticipated. Guidance from the National Institute for Health Research (NIHR) indicates that a sample size of 30 is appropriate to answer the questions posed by a feasibility trial [23]. A lower number of participants will be better suited for an educational intervention for clinicians — it will ensure delivery of a high-quality learning experience and allow for active engagement with tutors during problem-based learning within the experimental group. Furthermore, the stakeholder focus groups including of clinicians and educators reviewed the proposed sample size and reported it as appropriate for the feasibility trial.

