### Data collection, management, and analysis

In line with accepted practice for feasibility studies, no power analysis will be conducted, and all analyses will be exploratory only [29]. Data analysis will be performed after the last trial participant has completed final assessments (outcomes at 4 months post intervention). Data will be managed initially in Microsoft Excel software and analysed using IBM SPSS statistics software. Table 3 provides a summary of outcome measures, hypotheses, and analysis planned in the study.

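### Table 3 names the Kruskal–Wallis test for Knowledge and Skills without a contrast; it cannot serve the within-group or arm-by-time questions and does not itself give a confidence interval

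*Protocol article*

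**What the plan says.** The Knowledge and Skills rows of Table 3 carry the same method entry: "Effect sizes and 95% CIs from repeated measures ANOVA test and Kruskal–Wallis" H-test. Each row has three parallel hypotheses; for Knowledge they are "EG will have improved knowledge scores relative to CG EG will increase knowledge scores EG will maintain knowledge scores". The first compares the arms. The second and third follow the experimental group over time.

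Under Trial design the article states "This will be a two-arm feasibility randomised controlled trial with an experimental and control group" and "A repeated measures design will be adopted, whereby participants will complete outcome measures at baseline, immediately after the intervention, and at 4 months". Under Sample size, "the target sample size will be of a minimum 12 participants per trial arm; therefore, a minimum of 24 in total is anticipated". Under Data collection, management, and analysis, "no power analysis will be conducted, and all analyses will be exploratory only".

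Kruskal–Wallis appears only in Table 3. The abstract names a two-way mixed ANOVA as the quantitative model. Data management and research governance takes the range of potential effect sizes from repeated measures ANOVA alone. No section says which contrast the rank test addresses.

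**The concern.** Kruskal–Wallis compares independent groups. Two of the three hypotheses in each row compare the same people at different times, so its independence assumption fails for them. The only independent groups in the design are the two arms, and for two groups the test is the Mann–Whitney test. It has no arm-by-time term, which is the effect a repeated measures trial is built to estimate. It returns H and a p-value, whereas the cell promises effect sizes with intervals.

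The article's objectives include defining the sample size of a definitive trial, and the effect sizes on these outcomes would feed that. An analyst who took the three timepoints as the three groups would run a test that rarely rejects. That could hide real learning, and it could make a non-significant result look like support for "EG will maintain knowledge scores".

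**Working it through.** The article gives no alpha, SD, correlation or target effect for these outcomes, so there is no stated figure to reproduce. The check has two parts: which hypotheses the test can serve, and what a misapplied or unadjusted use would cost.

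**Part 1. Test against hypothesis**

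| Question in Table 3 | Observations compared | Can Kruskal–Wallis serve it? |
|---|---|---|
| Experimental versus control | Two independent arms | Yes, at one timepoint or on change scores; same as Mann–Whitney |
| Experimental group increases | Same people over time | No, observations are dependent |
| Experimental group maintains | Same people over time | No, observations are dependent |
| Arm-by-time effect (implied by the mixed ANOVA) | Six arm-by-time cells, dependent within person | No, there is no interaction term |

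**Part 2. Simulation**

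Inputs from the article: 12 per arm (2 × 12 = 24), two arms, three measurements per person. Assumed inputs: normal scores with SD 1, equal correlation ρ between timepoints, nominal two-sided 5%, a gain of 0.8 SD at both later timepoints for the within-group case, and an arm effect of 1 SD for the between-arm case. The main set used 10,000 runs; other sets used 5,000 to 8,000.

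*Across the three timepoints in one arm (10,000 runs).* Rejection is p < 0.05.

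| ρ | Type I error, Kruskal–Wallis | Type I error, Friedman | Power, Kruskal–Wallis | Power, Friedman |
|---|---|---|---|---|
| 0.3 | 2.0% | 6.0% | 41% | 51% |
| 0.5 | 0.5% | 5.9% | 40% | 66% |
| 0.7 | 0.1% | 5.9% | 37% | 86% |
| 0.9 | 0.0% | 5.8% | 36% | 100% |

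Repeat sets gave Kruskal–Wallis a type I error of about 0.7% at ρ = 0.5 and below 0.1% at ρ = 0.7. Its power was 36% to 39%, and Friedman's was 65% to 66% at ρ = 0.5 and 86% to 87% at ρ = 0.7. Repeated measures ANOVA reached 76% to 77% at ρ = 0.5 and 94% to 95% at ρ = 0.7. The mechanism is simple: the variance of a within-person difference is 2(1 − ρ)SD². The test behaves as if ρ were 0, so it overstates the noise by a factor 1/(1 − ρ), which is 2 at ρ = 0.5 and 3.3 at ρ = 0.7.

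*Pooled over the six arm-by-time cells.* With the same 0.8 SD gain in both arms, so no arm effect at all, the test rejected in 58% to 59% of runs. It responds to the common time trend and says nothing specific about the arms.

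*Between the two arms.* On change from baseline, type I error was 4.9% to 5.6%, so this use holds its level. For a 1 SD effect at one timepoint, ignoring baseline, power was 63%. On change scores it was 64% at ρ = 0.5 and 84% to 85% at ρ = 0.7. With baseline adjustment (ANCOVA) it was 74% to 75% at ρ = 0.5 and 89% at ρ = 0.7.

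**The case against.** The strongest reply is that Table 3 never assigns Kruskal–Wallis to the repeated timepoints. A reader might infer that use, because a test for three or more groups looks odd in a two-arm trial, but that is inference and the article does not say it. The type I errors across timepoints describe one possible misuse and not the plan. This stands.

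A reader might also infer that Table 3 promises something it cannot produce. The documents do not support that either. Repeated measures ANOVA is in the same cell, the analysis text draws effect sizes from it alone, and it also serves the within-person hypotheses. The entry can be read as ANOVA estimates plus a supplementary rank test. A rank effect size with a bootstrap interval could be derived as well.

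Nor is baseline necessarily discarded. The re-test section puts the focus on changes from baseline, and on change scores much of the power loss at ρ = 0.7 disappears, though about 10 points remain at ρ = 0.5. A rule for choosing between parametric and rank results commonly sits in the analysis plan, which is not shown, so its absence is not counted here.

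The feasibility decision rests on recruitment, retention and engagement, not on these tests. Finally, allocating staff of the same trust together casts doubt on independence between participants for ANOVA and Kruskal–Wallis alike, so it does not separate the two.

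What remains is that a named test is set against hypotheses most of which it cannot address, with its one valid use left unnamed.

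**Conclusion.** The point holds as a minor one. Kruskal–Wallis cannot address the within-group hypotheses or the arm-by-time effect. Between arms it is valid but no more than Mann–Whitney, and it does not itself yield an interval. The article leaves its contrast open.

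For ρ of 0.5 to 0.7, use across timepoints would give a type I error of about 0.1% to 0.7%. Power would be about 36% to 40%, against about 65% to 87% for Friedman and 76% to 95% for repeated measures ANOVA. A between-arm comparison at one timepoint would have about 63% power, against 74% to 89% with baseline adjustment.

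All of these figures rest on assumed correlations, effects and normal scores; only the 12 per arm, the two arms and the three measurements come from the article. The consequence is limited because the outcomes are secondary, the analyses are declared exploratory, and the planned ANOVA can supply the estimates.

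**What to change.** In the Knowledge and Skills cells of Table 3, replace Kruskal–Wallis with:

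- a baseline-adjusted between-arm difference with 95% CI at each follow-up;
- as the rank-based alternative, a Hodges–Lehmann shift with 95% CI on change from baseline between arms;
- Wilcoxon signed-rank (two timepoints) or Friedman (three) for any rank-based statement within the experimental group.

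If the authors prefer to keep a rank test between arms, they should call it Mann–Whitney and state the contrast and timepoint. The cost is two table cells and a matching sentence in the analysis text. It needs no new data, since baseline scores are already collected.
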